If more than 50% of parents or guardians on a selected team decline participation, that team will be replaced by another eligible team from the same school, which will inherit the school’s randomized condition to preserve the integrity of the cluster randomization. No re-randomization will occur at the team level. Parents or guardians of student-athletes in the waitlist control condition will receive similar study information but will be informed that their child(ren) will complete online surveys across the season and gain access to the TN mobile application after the season ends.

For the intervention group, a 30 min online pre-season training will be offered to orient participants to TN, including installation, initial setup, and core functions. Both the intervention and control groups will complete online surveys at three time points: the beginning of the season (baseline), mid-season, and the end of the season. Before each survey, participants will be reminded that their participation is voluntary, that they may withdraw at any time without penalty, and that their responses will be anonymous and not shared with coaches, parents, or school staff.

All survey data will be de-identified and stored on encrypted servers, accessible only to the research team. Coaches will not have access to individual student responses, only to aggregated, anonymized team-level summaries where appropriate. Neither personal-level data will be visible to schools nor to the TN developers.

Within two weeks of the postseason, coaches and student-athletes in the control group will be introduced to TN through a short tutorial and guided installation instructions via email. The study protocol and all related materials will be reviewed and approved by the Institutional Review Board prior to participant recruitment. All procedures will be conducted in accordance with the ethical principles outlined in the Declaration of Helsinki.

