### 2.5. Participant Support and Safety

While TN was not developed for clinical or diagnostic purposes, participant safety and mental well-being will be prioritized throughout the study. The platform includes a “Resources” page in both coach and student-athlete versions, linking users to publicly available mental health support materials, national helplines, and school-based counselors. A medical disclaimer is displayed upon login, stating that the platform does not provide crisis counseling or clinical assessment.

During pre-season orientation, the research team will review support and safety procedures with coaches and student-athletes. Participants will be informed that their app use and survey responses are confidential and not monitored in real time. Coaches will not have access to individual-level data or well-being responses and will not “track” specific student-athletes’ moods or app activity. Instead, any optional check-in features within TN are anonymized and used only for aggregate research analyses conducted by the research team.

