A tiered escalation protocol will be in place for any concerning responses that emerge in the study’s online surveys (e.g., endorsement of severe distress, self-harm intent, or perceived safety threats):Automated flagging: Surveys containing keywords or responses suggesting imminent risk will automatically generate a confidential alert to the principal investigator. Automated flagging is triggered by the presence of predefined keywords and phrases commonly associated with acute psychological distress or self-harm risk. Examples include references to suicidal ideation (e.g., “I want to kill myself,” “I don’t want to be here anymore”), self-harm behaviors (e.g., “cutting,” “hurting myself”), or imminent safety concerns (e.g., “I plan to hurt myself today”). These examples are illustrative rather than exhaustive. Flagging serves solely as an initial screening mechanism to prompt human review and does not initiate any automated decision-making or intervention.Review: The investigator will review flagged responses within 24 h to determine whether escalation is warranted.Referral and documentation: If a credible concern for participant safety is identified, the investigator will contact the school counselor to initiate a standard welfare check, following district safety procedures. No information will be shared with coaches or peers. When escalation is deemed necessary, only the minimum information required to support participant safety is shared with the designated school counselor. This information is limited to the nature of the concern (e.g., indication of severe distress or self-harm risk), the participant’s school affiliation, and the timing of the flagged response. No raw survey responses, application usage logs, or simulated conversation content will be shared. All communications follow established district welfare-check procedures, and identifying information will be disclosed only to authorized school liaison directly responsible for student support.Record keeping: All flagged cases and follow-up actions will be documented in a secure file accessible only to the principal investigator. Records will be deleted four weeks after the study concludes.

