#### 2.7.3. Data Protection & LLM Vendor Risk

All data management procedures comply with U.S. federal and institutional standards for research involving minors. TN uses Firebase Authentication and Firestore only for secure, cloud-based storage of de-identified metadata (e.g., session timestamps and feature usage metrics). No personally identifiable information, such as names, contact details, school identifiers, or chat content, is stored or transmitted.

When the application interacts with external LLM services via API calls, no identifiable or user-generated text leaves the device. Simulation prompts are pre-constructed from standardized, non-personal templates to generate consistent, de-identified responses. No raw conversation data from coaches or student-athletes is transmitted to, stored by, or retained on any external LLM vendor’s servers.

All LLM API providers used for this study (e.g., Together API/Ollama) are contractually required to exclude all request and response data from model-training or retention pipelines. No data transmitted through these APIs is logged, cached, or stored beyond the brief period required for real-time response generation.

All communications between the app, Firebase, and LLM endpoints occur via encrypted HTTPS (TLS 1.3) connections. Data stored within Firebase are encrypted at rest (AES-256) and hosted on U.S.-based Google Cloud servers compliant with ISO 27001 standards ([Bibr B16-behavsci-16-00268]). Access is restricted to authorized research personnel through institutional Google Workspace accounts with multi-factor authentication.

The study adheres to the Family Educational Rights and Privacy Act (FERPA) and the Children’s Online Privacy Protection Act (COPPA), ensuring that no education records or identifiable minor data are collected or disclosed. Because no raw conversational data are stored, retained, or transmitted, a Data Processing Agreement (DPA) with Firebase/Google and a Business Associate Agreement (BAA) or equivalent assurance from the LLM vendor confirms compliance with applicable data-protection standards.

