A standardized escalation procedure (SOP) is in place for any participant who reports risk of harm or distress during the study. Suppose a student-athlete indicates suicidal ideation, self-harm, or significant emotional distress in any survey or communication. In that case, the research team will immediately notify the designated school counselor or mental-health lead, following the IRB-approved safety protocol. The counselor will then initiate appropriate follow-up in accordance with district policy. No automated system decisions are made by the app, and no identifiable data are transmitted to LLM vendors during this process.

No persistent data is retained beyond anonymized metadata (such as login information) required for system functionality. Participants may delete their account associated with their anonymized IDs at any time.

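### Athletes are promised anonymity and no sharing with school staff, yet the safety escalation must identify a flagged minor to a school counselor, and section 2.5 contradicts itself on whether identity is passed on

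*Protocol article*

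**What the plan says.** Section 2.4 (Procedure) describes the reminder given before each of the three surveys. Besides voluntariness and the right to withdraw, athletes are told that "their responses will be anonymous and not shared with coaches, parents, or school staff". The next paragraph adds: "Neither personal-level data will be visible to schools nor to the TN developers". Section 3 (Limitations) says again that anonymity will be stressed to participants.

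Section 2.5 (Participant Support and Safety) uses a different term for the same data. Participants are told that "their app use and survey responses are confidential and not monitored in real time".

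The tiered escalation in section 2.5 then has the investigator review flagged survey responses within 24 hours, and states: "If a credible concern for participant safety is identified, the investigator will contact the school counselor to initiate a standard welfare check". On what the counselor receives, it says "This information is limited to the nature of the concern", with the participant's school and the timing of the response as the only other items. It rules out passing on raw survey responses. Shortly afterwards it says that "identifying information will be disclosed only to authorized school liaison directly responsible for student support".

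Section 2.7.3 (Data Protection & LLM Vendor Risk) describes the study as "ensuring that no education records or identifiable minor data are collected or disclosed". Later in the same section, if an athlete indicates suicidal ideation, self-harm or significant distress, "the research team will immediately notify the designated school counselor or mental-health lead".

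**The concern.** The statements conflict on two levels. First, a survey that is anonymous and closed to school staff cannot also lead a school counselor to a particular student. Second, within section 2.5, a closed list containing no identifier sits beside a sentence that assumes identifying information is released.

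The participants are aged 14 to 18, parental consent is planned as opt-out, and the surveys ask about hopelessness and uncontrollable worry, so a disclosure of distress is foreseeable. Followed as written, either a minor who reports risk of self-harm cannot be located by the person sent to help, or that minor answered under an assurance that was not true.

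**Working it through.** The plan gives no figure on this point to reproduce. The check is a comparison of the statements, with simple arithmetic for scale.

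**Assurance against escalation**

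| Question | Assurance | Escalation |
|---|---|---|
| Can a response be traced to a person? | No: described as anonymous (2.4, 3) | Yes: an individual welfare check follows a survey response (2.5, 2.7.3) |
| Does school staff learn anything? | No: not shared with school staff, nothing person-level visible to schools (2.4) | Yes: the school counselor or mental-health lead is told (2.5, 2.7.3) |
| Is there a safety exception? | None stated in the reminder | Disclosure is the purpose of the procedure |

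Section 2.5 closes by saying that a participant identified as at risk will be put in touch with school-based support. That is possible only if the school knows who the participant is.

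**Section 2.5 against itself**

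The closed list holds three facts: nature of the concern, school, timing. None identifies the student. The later sentence restricts who may receive identifying information, which presupposes that someone does.

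- *If the closed list governs*, the counselor knows the school but not the student. With two teams per school (2.2) and about 15 to 25 athletes per team (2.3), the student is one of 2 × 15 = 30 to 2 × 25 = 50.
- *If the disclosure sentence governs*, the student is known, but the reminder in 2.4 is then untrue for that student, and so, on its wording, is the statement in 2.7.3 about identifiable data on minors.

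**Reach of the assurance**

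- Athletes: 4 × 15 = 60 to 4 × 25 = 100.
- Reminders over three surveys: 3 × 60 = 180 to 3 × 100 = 300. This is an upper bound that assumes every athlete takes every survey.

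These figures count how often the statement is made. They do not measure harm.

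**Two secondary points**

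- *Linkage.* Section 2.9 uses repeated measures and enters each outcome's baseline value as a covariate, so each athlete's surveys must be linked. The data are therefore coded. A name-free code would serve the analysis; only the escalation needs a key back to the person.
- *Threshold and timing.* Section 2.5 allows up to 24 hours for review, followed by a judgement on credibility. Section 2.7.3 calls for immediate notification once risk is indicated. The two can be partly reconciled if the second is taken to start after the first, but the text does not say so.

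**The case against.** The strongest reply is that section 2.5 can be read as a whole: the closed list governs what is said about the concern, and the later sentence governs who may learn the identity. On that reading the counselor can find the student. This is plausible, and it weakens the claim that the student could not be located. It does not rescue the plan, because identity and a concern drawn from the survey then reach school staff, which the reminder says will not happen.

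Several softening points are fair as far as they go:

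- Raw responses are not passed on, so the promise misleads by omission more than by releasing answers. But the nature of the concern comes from the answer, and identity is what the word anonymous excludes.
- Section 2.4 calls the survey data de-identified, so anonymous may be loose wording. The athletes are nonetheless told anonymous.
- Safety procedures are reviewed at a pre-season orientation. The text does not say that this covers the exception, and does not make clear that control athletes attend. The reminder before each survey omits it either way.
- The sentence in 2.7.3 on identifiable data mainly concerns the app. Its subject is the study, so the wording is too broad, but the conclusion does not depend on it.
- The assent form and parent letter are not shown and may state the exception. That would not correct the reminder as the article describes it.

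It is also true that the number of athletes who would be escalated is unknown, that the article never says outright that a name is given, and that no analysis result changes.

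**Conclusion.** The concern holds. Statements the protocol makes outright contradict each other; nothing here rests on detail an article might leave out. The unqualified promise in section 2.4 cannot stand beside the escalation in sections 2.5 and 2.7.3, and section 2.5 is inconsistent on whether identity is passed on. Depending on which sentence is followed, the counselor is left with 30 to 50 candidates or the assurance is untrue for the flagged student.

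This rests on two readings: that a school counselor counts as school staff, and that a welfare check on an individual requires that individual's identity. The counts assume the stated team sizes. The matter must be fixed before recruitment because it concerns the accuracy of assent and the safety of minors. The linkage and timing points are secondary.

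**What to change.** 1. In sections 2.4 and 3, and in any participant material with the same wording, replace anonymous with *confidential, linked by a study ID*. This also matches the term in section 2.5. The research team alone holds the key from ID to name, stored apart from the survey data.
2. State the exception in the reminder and the assent, for example: *not shared with coaches, parents or school staff, except that your identity and the nature of the concern will be given to the designated school counselor if there is a safety concern*. Attach the same exception to the sentence in 2.4 on what schools can see. In 2.7.3, say that app data hold no identifiers and that the survey linkage key is the exception.
3. In section 2.5, add the student's identity to the list of information given to the counselor.
4. Give sections 2.5 and 2.7.3 one threshold and one time limit. The clinical content is for the investigators and the IRB to set before recruitment.

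The cost is wording changes to the protocol, assent and survey reminder, inclusion in the IRB submission, and a secured linkage file. The drawback is that athletes may answer a little less candidly once they know the surveys are confidential with a safety exception.

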### 2.5. Participant Support and Safety

While TN was not developed for clinical or diagnostic purposes, participant safety and mental well-being will be prioritized throughout the study. The platform includes a “Resources” page in both coach and student-athlete versions, linking users to publicly available mental health support materials, national helplines, and school-based counselors. A medical disclaimer is displayed upon login, stating that the platform does not provide crisis counseling or clinical assessment.

During pre-season orientation, the research team will review support and safety procedures with coaches and student-athletes. Participants will be informed that their app use and survey responses are confidential and not monitored in real time. Coaches will not have access to individual-level data or well-being responses and will not “track” specific student-athletes’ moods or app activity. Instead, any optional check-in features within TN are anonymized and used only for aggregate research analyses conducted by the research team.

A tiered escalation protocol will be in place for any concerning responses that emerge in the study’s online surveys (e.g., endorsement of severe distress, self-harm intent, or perceived safety threats):Automated flagging: Surveys containing keywords or responses suggesting imminent risk will automatically generate a confidential alert to the principal investigator. Automated flagging is triggered by the presence of predefined keywords and phrases commonly associated with acute psychological distress or self-harm risk. Examples include references to suicidal ideation (e.g., “I want to kill myself,” “I don’t want to be here anymore”), self-harm behaviors (e.g., “cutting,” “hurting myself”), or imminent safety concerns (e.g., “I plan to hurt myself today”). These examples are illustrative rather than exhaustive. Flagging serves solely as an initial screening mechanism to prompt human review and does not initiate any automated decision-making or intervention.Review: The investigator will review flagged responses within 24 h to determine whether escalation is warranted.Referral and documentation: If a credible concern for participant safety is identified, the investigator will contact the school counselor to initiate a standard welfare check, following district safety procedures. No information will be shared with coaches or peers. When escalation is deemed necessary, only the minimum information required to support participant safety is shared with the designated school counselor. This information is limited to the nature of the concern (e.g., indication of severe distress or self-harm risk), the participant’s school affiliation, and the timing of the flagged response. No raw survey responses, application usage logs, or simulated conversation content will be shared. All communications follow established district welfare-check procedures, and identifying information will be disclosed only to authorized school liaison directly responsible for student support.Record keeping: All flagged cases and follow-up actions will be documented in a secure file accessible only to the principal investigator. Records will be deleted four weeks after the study concludes.

This protocol ensures that any participant identified as potentially at risk is connected promptly to appropriate, school-based mental health support while maintaining confidentiality and adhering to ethical standards. All personnel involved in data collection will complete human subjects research ethics training prior to study initiation.

### 2.6. Coach and Student-Athlete Interviews

To complement the quantitative data, brief semi-structured interviews will be conducted at the end of the season with a purposive subsample of coaches (*n* = 2) and student-athletes (*n* = 6) to gather exploratory, usability-focused feedback on the TN platform’s interface, acceptability, and perceived impact on team culture and well-being. An interview guide with open-ended questions developed by the research team will be used to elicit user experiences, perceived benefits and challenges, and recommendations for future iterations.

Interviews will be conducted in person or via Zoom, depending on participants’ preferences. With consent, interviews will be audio-recorded, transcribed verbatim, de-identified, and reviewed for transcription accuracy. Participation in interviews will be voluntary. Confidentiality will be protected by using pseudonyms in transcripts and reports. No identifying information will be shared with schools. Participants may withdraw at any time without penalty.

Given the pilot nature of the study and its emphasis on feasibility, acceptability, and user experience, a small number of interviews are deemed appropriate to identify salient interface- and experience-related issues that may inform future refinement of the platform. Student-athletes will be selected for interviews using purposive sampling to capture a range of perspectives based on variation in sport type, self-reported engagement with the application, and observed patterns of app use over the season.

### 2.7. App-Based Intervention Development

TN was developed as a cross-platform mobile tool using React Native version 0.83 with Expo for the frontend, enabling deployment across iOS devices and other platforms. The backend was implemented in Python 3 using Flask, connected to a Firebase Firestore database for secure storage of anonymized user data, including session logs and survey completion records. The application delivers simulated coach–athlete conversations, powered by LLMs, and hosted via external Application Programming Interface (APIs). Each simulation presents the participant with a dynamic student-athlete persona characterized by varying motivational styles, challenges, and attitudes. Simulated student-athlete responses vary based on selected settings. See examples of two Simchat dialogues below:(1)*Coach* (*human*): “Hey, how are you feeling lately?”*Athlete* (*AI*): “I’ve been stressing out a lot about the upcoming game. Just hoping everything goes smoothly.”*Coach* (*human*): “You’re doing great. I have full confidence in you. Can’t wait to see what you do this weekend.”*Athlete* (*AI*): “I know you believe in me, but I just can’t shake this nervousness. What if I mess up in front of everyone? Coach, can we talk about some strategies to calm down before the game? To be honest, I’m really worried.”

(2)*Coach* (*human*): “Hey, how are your feeling lately?”*Athlete (AI):* “I’ve been okay, just trying to stay focused on the games. Got a big match coming up, so I’m trying to manage my nerves.”*Coach* (*human*)*:* “I appreciate your focus and dedication to our team. Is there anything I can do to help calm your nerves?”*Athlete* (*AI*): “I’ve been practicing deep breathing exercises, helps a bit. Just need to stay positive and believe in the team.”

From an implementation perspective, TN is deployed as a modular client–server system designed for scalability and minimal data exposure. The mobile client, built with React Native and Expo, handles user interaction, local state management, and on-device preprocessing (including lightweight redaction). A Python-based Flask backend manages authentication, session orchestration, and secure communication with external services. Anonymized metadata and usage logs are stored in Firebase Firestore, while simulated conversation responses are generated via external LLM APIs using standardized, non-personal prompt templates. This separation of concerns allows core application logic, data storage, and language-model inference to operate independently, reducing system complexity and supporting secure deployment in school-based settings.

